## Data entry and analyses

This trial aims to provide replicated evidence that MST is as effective as ECT in terms of remission rates, response rates, and reduction of depressive symptoms (assessed by the primary outcome: change in HDRS-24 from baseline to 12-week follow-up after the acute treatment phase) and superior in preserving verbal memory (via HVLT-R as an additional primary outcome), with fewer physical and cognitive side effects overall. Additionally, this study will explore personalized electrophysiological indicators (EEG/ECG) in an exploratory manner to inform future individualized treatment decisions for ECT and MST, and to generate hypotheses about the physiological mechanisms underlying the antidepressant efficacy and cognitive effects of MST/ECT. To our knowledge, this will be the largest RCT comparing ECT and MST in China. The trial will provide evidence to determine whether individualized treatment decisions based on personalized electrophysiological characteristics hold promise for optimizing the balance between efficacy and side effects (40). Specifically, it will offer insights into the potential effect sizes, acceptability, feasibility, and safety of the novel interventions under investigation. Predicting efficacy and side effects based on physiological characteristics, such as indicating greater side effects with ECT and comparable efficacy but fewer side effects with MST for patients with MDD, suggests that MST may be more suitable for these patients. Alternatively, physiological characteristics indicating superior efficacy with ECT compared to MST, with comparable side effects between the two, suggest that ECT may be more appropriate for these patients.

Firstly, data entry will undergo a thorough double-check to ensure accuracy. Data quality will then be assessed, with particular attention given to data distribution, and outliers will be excluded from subsequent analysis. Once data integrity is confirmed, detailed analyses of primary and secondary outcomes will be conducted using IBM SPSS Statistics 20 for Windows (Armonk, NY: IBM Corp).

Descriptive statistics, such as mean and standard deviation, will be computed for each study arm separately. Analyses will be performed within the intention-to-treat (ITT) framework to assess the effectiveness of interventions for all participants, utilizing multiple imputed datasets to address missing data.

Appropriate statistical methods will be employed for data analysis, including mixed-effects models for repeated measures (MMRM). MMRM with a factorial design (3 time points × 2 conditions) will be conducted to examine significant interactions between time (baseline, Day 30, and Week 12) and condition (ECT and MST), while adjusting for potential covariates such as age, sex, duration of illness, age of onset, IQ, and antidepressant usage. This approach is robust to missing data under the missing-at-random (MAR) assumption and provides unbiased estimates of treatment effects. The significance level will be set at 0.05.

Sensitivity analyses will be performed to assess the robustness of results to missing data, including multiple imputation (MI) under MAR and missing-not-at-random (MNAR) assumptions. Results from MMRM and MI will be compared. Exploratory analyses will include subgroup analyses by demographic/clinical characteristics and correlation analyses between neurophysiological biomarkers (EEG/ECG) and treatment outcomes, using linear or logistic regression models as appropriate.

Subgroup analyses will compare relapse rates and time-to-relapse between participants who received maintenance treatments versus those who did not, within both MST and ECT groups. This will help disentangle the effects of acute treatment from post-treatment management strategies.

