### Outcomes

#### Primary outcome

The primary outcome measure is the change in HDRS-24 total score from baseline to the 12-week follow-up, which is assessed after the completion of the 12-session acute treatment phase (conducted over 4 weeks) and a subsequent 12-week post-treatment observation period. A reduction of at least 50% in the HDRS-24 score indicated a response to treatment, while a reduction of at least 60% in the HDRS-24 score and a total score of 8 or less indicated remission. Change in HVLT-R total recall score from baseline to the 12-week follow-up (assessing verbal memory, a key cognitive domain sensitive to seizure therapy effects).

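### Excluding outliers found from the data distribution before the primary and secondary analyses conflicts with intention-to-treat and can bias the comparison in either direction

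*Protocol article*

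**What the plan says.** The section Data entry and analyses of the protocol article sets out a sequence. First, "data entry will undergo a thorough double-check to ensure accuracy". The next step is a review of quality that looks especially at how the values are distributed, and its result is that "outliers will be excluded from subsequent analysis". The outcome analyses come only after this: "Once data integrity is confirmed, detailed analyses of primary and secondary outcomes will be conducted".

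The section goes on to define the analysis set: "Analyses will be performed within the intention-to-treat (ITT) framework to assess the effectiveness of interventions for all participants". For missing values it plans multiple imputation. On robustness it says: "Sensitivity analyses will be performed to assess the robustness of results to missing data". It names no analysis that keeps the outliers in.

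Under Primary outcome, "The primary outcome measure is the change in HDRS-24 total score from baseline to the 12-week follow-up". Change in HVLT-R total recall over the same interval is the additional primary outcome. The outlier sentence is not restricted to any class of variable, so it covers both.

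**The concern.** Entry accuracy has its own earlier step. The exclusion that follows is triggered by where a value lies in the distribution, not by evidence that it is wrong. A correctly recorded score from a patient who did unusually badly, or unusually well, can be removed.

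Three things are at stake.

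- **Analysis set.** Dropping a randomised patient, or a valid score, because of the outcome value is not an intention-to-treat analysis of all participants.
- **Missing-data assumption.** If the excluded scores were set to missing and imputed, patients would stay in the set, but observed results would be replaced by model draws. The missingness would depend on the value itself, which is contrary to the missing-at-random assumption stated for the mixed model.
- **Design.** This is a non-inferiority trial. Anything that shrinks a real difference, or shrinks its standard error, makes non-inferiority easier to declare. An exclusion settled after seeing the distribution leaves room for choices that affect both.

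**Working it through.** **The plan's own figures.** None is attached to the outlier rule. The sample size is a separate matter: G*Power's total of 166 reproduces (λ = 166 × 6 × 0.1² / (1 − 0.5) = 19.92; df 5 and 820; power 0.950), and 166 / 0.8 = 207.5, so 208 against 210 planned. The fix leaves it unchanged.

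**Reading the text.** The order is entry check, distribution review, exclusion, outcome analysis. Artefact handling for EEG and ECG is described in its own sections, so the sentence cannot be confined to those signals. The conflict with analysing all participants follows from the text alone.

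**Illustration 1: effect on the difference.** All distributions are assumptions. HDRS-24 change is N(−18, 6) in most patients and N(+2, 5) in failures. The true difference (MST minus ECT, positive meaning MST worse) is

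(2 − (−18)) × (p_MST − p_ECT) = 20 × (0.15 − 0.05) = 2.0.

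At 20% against 10% it is again 20 × 0.10 = 2.0. The third case takes the response rates quoted under Sample size estimation (51.4% MST, 42.1% ECT), so non-response is 100 − 51.4 = 48.6% and 100 − 42.1 = 57.9%. The higher rate is assigned to MST so that there is a deficit to hide: 20 × (0.579 − 0.486) = 1.86, simulated as 1.85. Mean differences after exclusion, from simulations of at least 400,000 per arm (simulation error of a few hundredths):

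| Failures MST v ECT | Before | Cut-offs | 1.5 IQR | 2 SD | 3 SD |
|---|---|---|---|---|---|
| 15% v 5% | 2.0 | pooled | 0.86 | 0.69 | 1.80 |
| 15% v 5% | 2.0 | per arm | 1.67 | 1.50 | 2.26 |
| 20% v 10% | 2.0 | pooled | 1.35 | 1.19 | 1.96 |
| 20% v 10% | 2.0 | per arm | 2.74 | 2.25 | 2.19 |
| 57.9% v 48.6% | 1.85 | pooled | 1.85 | 1.83 | 1.85 |
| 57.9% v 48.6% | 1.85 | per arm | 1.85 | 2.07 | 1.85 |

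Pooled cut-offs with rare failures shrink the deficit because they remove more from the worse arm (15% v 5%, IQR rule: 8.0% of MST against 2.8% of ECT). Per-arm cut-offs can do the opposite: failures stretch the limits in the arm that has more of them, so more are removed from the better arm.

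**Illustration 2: effect on the error rate.** This uses 105 per arm, 4,000 runs and improvement scores. The margin is set equal to the true deficit, so the nominal chance of declaring non-inferiority is 0.025. The article states no margin; this one is an assumption.

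| Assumed data | Rule | Difference | SE | P(declare NI) |
|---|---|---|---|---|
| Normal, SD 8, MST worse by 3 | pooled 2 SD | 3.00 → 2.37 | 1.10 → 1.00 | 0.026 → 0.097 |
| Same | per-arm 2 SD | 2.98 → 2.99 | 1.10 → 1.00 | 0.026 → 0.054 |
| Failures N(−10, 4), others N(16, 6); 10% MST v 3% ECT | pooled 1.5 IQR | 1.82 → 0.05 | 1.19 → 0.85 | 0.031 → 0.556 |
| Same | per-arm 3 SD | 1.81 → 2.08 | 1.19 → 1.11 | 0.030 → 0.052 |
| Failures N(4, 5), others N(20, 5); 50% MST v 40% ECT | pooled 1.5 IQR | 1.58 → 1.58 | 1.29 → 1.29 | 0.025 → 0.025 |

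In the second and fourth rows the difference does not shrink, yet the error rate about doubles, because trimming makes the standard error too small.

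**The case against.** A reader might infer that the rule removes true treatment failures, pulls the arms together and so favours MST. The documents do not support that. Nothing says that outliers are failures, that they cluster in one arm, or that cut-offs are pooled. In the trial cited for planning about half the patients did not respond. When failure is that common, ordinary non-responders are not distributional outliers, and the IQR and 3-SD rules change nothing. Per-arm rules can widen the deficit. Unusually good responders can also be excluded.

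Nor can one say that HVLT-R outliers would be the patients with the greatest memory loss. No calculation supports it, and large gains could equally be flagged. The article hopes to show MST superior on verbal memory, so dropping severe losses under ECT would work against MST. These objections stand, and no direction is claimed here.

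Two further objections stand in part. The sentence sits between data quality and data integrity, so it may have been meant as data cleaning, and it does not say whether values or patients go. Imputing the excluded values would soften the conflict with intention-to-treat, but would still replace genuine observations.

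Finally, thresholds and blinded data review commonly belong in an analysis plan, which is not shown, so their absence is not the point. The point is the rule that is stated. Defining an outlier more closely would not cure it, because any definition that excludes genuine scores from the primary analysis still conflicts with analysing all participants.

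**Conclusion.** The concern holds as a conflict within the text: an exclusion guided by the distribution, applied before the primary and secondary analyses, against an intention-to-treat analysis of everyone. That part needs no assumption.

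The consequence is a possible bias of unknown sign. In the illustrations a true difference of 2.0 ends anywhere from 0.69 to 2.74, and the chance of wrongly declaring non-inferiority runs from the nominal 0.025 up to 0.556. The upper figure is a worst case (rare failures concentrated on MST, pooled IQR rule), not a forecast. All these figures rest on assumed distributions, cut-offs and margins. Confidence is high on the conflict and low on the size or direction in this trial.

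**What to change.** Delete the outlier sentence for the clinical and cognitive outcomes and state instead that:

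- a value is corrected, or set to missing, only if a check against source shows it to be an error, and that decision is made blind to arm;
- all other observed values stay in the primary analysis, however extreme;
- any outlier rule or robust method (robust regression, for example) is prespecified and used only as a sensitivity analysis, reported beside the primary result.

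Signal artefact handling for EEG and ECG can stay as described in its own sections. The cost is a few lines of wording, with no change to sample size, visits or data collected. It should be settled before anyone sees outcomes by arm.

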### Study design

The present clinical protocol is designed as a double-blind, parallel, non-inferiority, randomized clinical trial.

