### Sample size estimation

The sample size calculation for this study was conducted through *a priori* power analysis using G*Power 3.1.9.7 (29). Parameters were chosen, including α = 0.05 and power (1-ß) = 0.95. An effect size of f = 0.1 was selected based on previous research findings (15). Specifically, in the intent-to-treat sample (N = 73), 18 participants (51.4%) in the MST group (N = 35) and 16 (42.1%) in the ECT group (N = 38) met response criteria, while 13 (37.1%) in the MST group and 10 (26.3%) in the ECT group met remission criteria. In addition to the two experimental conditions (MST and ECT), covariates including age, sex, duration of illness, age of onset, intelligence quotient (IQ), and antidepressant usage were considered, resulting in a total of 6 covariates. Accounting for a potential dropout rate of 20%, the final estimated number of participants required for the study was determined to be 210. (**Figure 2**).

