MST will be conducted at 100 Hz and 100% output using a pulse width of 350 μs and a peak intensity of the magnetic field at 3.0 Tesla. The duration of magnetic stimulation will be titrated using a 10-second train duration, starting from 2 seconds and increasing by 4 seconds in subsequent sessions, up to a maximum of 10 seconds (i.e., 200–1,000 pulses per session). In cases of poor seizure quality (<15 s), the stimulation duration increment will be set to 6 seconds in the next session. If no seizures were elicited, an additional 10-second stimulation will be administered immediately. Subsequent MST treatments will be maintained at a 10-second duration for a total of 1000 pulses.

EEG recordings during MST and ECT will be obtained using the Thymatron IV device with left and right frontal leads.

Patients will undergo identical preparation procedures, including the placement of earplugs and skin preparation for ECT electrode placement, irrespective of treatment allocation. To maintain blinding, the auditory stimulus from a recorded MST session will be played during ECT administration to prevent treatment allocation disclosure to individuals in adjacent rooms.

Completers will be defined as patients who received at least 8 treatments or achieved remission before the eighth treatment. Relapse will be defined as an HDRS-24 total score of 16 or higher, with at least a 10-point increase in HDRS-24 score sustained across two visits at least 1 week apart, the emergence of psychotic or suicidal symptoms, or the need for readmission to inpatient care.

While 12 sessions are standard for acute-phase treatment, the potential need for more sessions in MST will be explored through *post-hoc* analyses. This trial’s design prioritizes comparability with ECT’s typical acute regimen while allowing for long-term outcome assessment to capture delayed benefits.

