### Additional treatments

As the primary objective of this trial is to evaluate efficacy, participants are restricted from receiving concurrent treatments for their depressive symptoms, except for one type of antidepressant medication, during the 30-day intervention period. However, the use of psychoactive medications and psychotherapy is allowed during the 12-week follow-up period, with detailed documentation of the type, dosage, and frequency/session of medication or psychotherapy.

During the 12-week follow-up period, participants may receive maintenance ECT, pharmacotherapy (e.g., antidepressants, mood stabilizers), or psychotherapy to prevent relapse. The type, dosage, and frequency of maintenance treatments will be recorded in detail to assess their impact on outcomes.

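### The non-inferiority claim rests on a single named population, ITT; the defined completers have no analysis, and the effect of follow-up treatment on Week-12 HDRS-24 is not addressed

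*Protocol article*

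**What the plan says.** All places are in the protocol article.

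- **Study design** calls the trial a "double-blind, parallel, non-inferiority, randomized clinical trial".
- **Primary outcome** is HDRS-24 change from baseline to the 12-week follow-up. HVLT-R total recall is an additional primary outcome.
- **Data entry and analyses**: "Analyses will be performed within the intention-to-treat (ITT) framework to assess the effectiveness of interventions for all participants", with multiple imputation for missing values. The model is an MMRM with baseline, Day 30 and Week 12, and "The significance level will be set at 0.05". The sensitivity analyses are imputation under MAR and MNAR. The planned comparison by maintenance treatment covers relapse and time to relapse within each arm, not the HDRS-24 contrast between arms.
- **ECT and MST procedures**: "Completers will be defined as patients who received at least 8 treatments or achieved remission before the eighth treatment". The term is not used again in the analysis text.
- **Withdrawal criteria**: fewer than 8 sessions within 30 days leads to withdrawal, but withdrawn patients are still followed for outcomes where this can be done.
- **Additional treatments**: during the 12-week follow-up "participants may receive maintenance ECT, pharmacotherapy (e.g., antidepressants, mood stabilizers), or psychotherapy to prevent relapse".
- **Secondary outcomes**: where rescue treatment is given before Week 12 (maintenance ECT is an example), outcomes are recorded up to that point, for time to relapse.

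**The concern.** In a superiority trial, anything that makes the arms more alike works against the claim. In a non-inferiority trial it works for the claim, so ITT alone is not the cautious choice. Two separate mechanisms are written into this plan.

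1. **Incomplete treatment.** Patients who stop early can still supply observed outcomes and enter ITT under-treated. If under-treated patients differ less between arms than fully treated ones, the estimated difference shrinks.
2. **Shared follow-up treatment.** The primary endpoint comes after 12 weeks in which both arms may receive the same treatments. An MST patient may receive the comparator before being scored.

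The planned robustness checks address missing values. Neither mechanism is a missing-value problem. At stake is whether a finding that MST is non-inferior reflects the treatments or the loss of contrast between them.

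**Working it through.** **1. The plan's own figure.** The sample size section states: "Parameters were chosen, including α = 0.05 and power (1-ß) = 0.95" and "An effect size of f = 0.1 was selected based on previous research findings". The Figure 2 caption adds 2 groups, 6 measurements, correlation 0.5 and sphericity correction 1.

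- Noncentrality λ = f² × N × m / (1 − ρ) = 0.01 × 166 × 6 / 0.5 = 19.92.
- Degrees of freedom: 5 and (166 − 2) × 5 = 820. Critical F = 2.22502; power = 0.9501.
- Dropout: 166 / 0.8 = 207.5, so 208. The plan's 210 is 7 centres × 30.

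The stated figure reproduces. It sizes an interaction test for a difference and contains no margin, so it gives no anchor for the effect of dilution.

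**2. What dilution does to a non-inferiority test.** Assumptions, none of them in the article: one-sided 2.5% test, 105 per arm, margin M in SD units, true MST disadvantage exactly M, and a share q of patients in whom expected outcome is the same in both arms.

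- SE = √(2/105) = 0.138 SD.
- Expected ITT difference = (1 − q) × M.
- Probability of a false non-inferiority claim = Φ(−1.96 + q × M / SE).

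Example: M = 0.4, q = 0.2 gives 0.2 × 0.4 / 0.138 = 0.58, and Φ(−1.38) = 8.4%.

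| Margin (SD) | q = 0 | q = 10% | q = 20% |
|---|---|---|---|
| 0.3 | 2.5% | 4.1% | 6.4% |
| 0.4 | 2.5% | 4.7% | 8.4% |
| 0.5 | 2.5% | 5.5% | 10.8% |

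With 84 per arm (105 × 0.8; SE = √(2/84) = 0.154), the 20% column becomes 5.8%, 7.5% and 9.5%. A simulation with 105 per arm, q = 20% and the margin at which the test has 90% power (0.447 SD) gave 9.3%; the formula gives 9.5%.

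**3. What a completer set would and would not remove.** Set side by side, the sections show three things.

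- Completer status depends only on the acute course. A patient who completes it and then receives maintenance ECT breaks no rule and stays in the set. The set therefore addresses mechanism 1, not mechanism 2.
- The completer and withdrawal definitions disagree. A patient who remits before the eighth session and stops is a completer under ECT and MST procedures but meets the first withdrawal criterion. The 30-day limit also appears only in the latter.
- Day 30 is already a model time point and precedes the follow-up period, so its contrast is not affected by mechanism 2.

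**4. HDRS-24 after follow-up treatment.** Secondary outcomes stops recording at rescue, for time to relapse. Additional treatments permits some of the same treatment with documentation only. Data entry and analyses covers all participants. Nothing says whether HDRS-24 values after such treatment count at Week 12 or are treated as missing, so the direct effect of mechanism 2 on the primary contrast is left open.

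**The case against.** The strongest reply is that this is a condensed article. Naming ITT does not exclude a supportive set, and a statistical analysis plan may give the completers a use. A reader might infer that the trial has ruled out a per-protocol analysis or that planning ITT is an error; the article supports neither. What remains is that it states a population, lists its sensitivity analyses and defines completers, and these parts as written leave the non-inferiority claim on one population.

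A second reply is that the completer set is itself biased. This is correct. Early remitters count as completers while non-remitters who stop before session 8 do not. If more MST non-responders stopped early, the set would favour MST. It can only support ITT.

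Third, a reader might take the 20% dropout allowance as evidence that 20% of outcomes are equalised. It is not. The allowance covers lost data, and values imputed under MAR do not by themselves dilute the difference. Nor does the article show that many patients will miss the assigned course.

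Fourth, the plan does include Day 30 in the model, MNAR analyses and maintenance subgroups. These help in part, but Day 30 is given no stated role in the non-inferiority conclusion, and the subgroups concern relapse only.

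Finally, without a margin no both-sets rule can be run. That is so, and the missing margin is a separate and larger gap.

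**Conclusion.** The point holds in limited form. For a non-inferiority claim, the article names ITT alone, gives its completers no analysis, and checks robustness to missing data only. Under-treatment can bias the comparison towards no difference, provided under-treated patients differ less between arms. Permitted follow-up treatment can do so separately, and a completer analysis would not cure it.

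The figures of about 4% to 11% instead of 2.5% are illustrations. They rest on an assumed 10% to 20% equalisation, assumed margins of 0.3 to 0.5 SD and an assumed one-sided 2.5% test. It would be tempting to read them as this trial's actual error rate; the article gives neither the margin nor the rates needed for that. The direction and the gap are well supported, the size is not. The change is worth making, but it ranks below stating a margin.

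**What to change.** In Data entry and analyses:

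1. Keep ITT and add a supportive per-protocol run of the same HDRS-24 model in patients who completed the acute course on the allocated device. First reconcile the completer definition in ECT and MST procedures with the rule in Withdrawal criteria.
2. Report the Day 30 between-arm contrast from the existing model as supportive.
3. Reconcile Secondary outcomes, Additional treatments and Data entry and analyses on how HDRS-24 values after maintenance or rescue treatment enter the Week-12 analysis.
4. Once a margin is stated, claim non-inferiority only if the ITT and per-protocol results agree.
5. Keep ITT as primary for the HVLT-R superiority comparison.

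The analysis cost is one further run of the same model; Day 30 is already in it. The price is a smaller set that randomisation does not protect and that can be biased either way. If every expected dropout were a non-completer, 84 per arm would remain. Power at no true difference would then fall from 82.6% to 73.6% for an assumed margin of 0.4 SD, and from 95.2% to 90.0% for 0.5 SD. Patients lost after completing the acute course would make the reduction in the set smaller.

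### Multiple imputation is named both as the intention-to-treat method and as a sensitivity analysis against the MMRM, so the primary HDRS-24 and HVLT-R estimates are not fixed

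*Protocol article*

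**What the plan says.** All the relevant text is under Data entry and analyses in the protocol article.

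- **General rule.** "Analyses will be performed within the intention-to-treat (ITT) framework to assess the effectiveness of interventions for all participants", and the same sentence ends with "utilizing multiple imputed datasets to address missing data". Nothing limits this to sensitivity analyses or to particular outcomes.
- **Model.** "MMRM with a factorial design (3 time points × 2 conditions) will be conducted to examine significant interactions". The time points are baseline, Day 30 and Week 12, with adjustment for six covariates.
- **Missing data in the model.** "This approach is robust to missing data under the missing-at-random (MAR) assumption and provides unbiased estimates of treatment effects". Here the handling of missing data is credited to the MMRM itself.
- **Sensitivity.** "Sensitivity analyses will be performed to assess the robustness of results to missing data, including multiple imputation (MI) under MAR". The sentence goes on to include missing-not-at-random (MNAR) assumptions.
- **Comparison.** "Results from MMRM and MI will be compared".

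Two other sections bear on this. Primary outcome names two measures, the change to the 12-week follow-up in HDRS-24 and in HVLT-R total recall. Clinical measures schedules ratings at baseline, after sessions 3, 6, 9 and 12, and at Weeks 4, 8 and 12. Cognitive assessments puts the cognitive tests at the same times.

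**The concern.** MI is given two incompatible roles: the method behind the intention-to-treat results, and the alternative against which the MMRM is tested. No sentence says which analysis yields the primary estimate for either primary outcome. Two things are at stake.

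First, an analyst holding both results could present either as the prespecified one and cite the text for it. In a non-inferiority comparison, a modest shift can matter when a confidence limit lies near the decision boundary.

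Second, the planned comparison can be misread. MMRM and MI under MAR both assume MAR. If they also use the same variables, close agreement is expected whether or not MAR is true, and reporting it as robustness would be wrong. The plan allows for 20% dropout, so the handling of missing Week 12 scores is not a side issue.

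**Working it through.** **1. The text, reading by reading.**

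| If the primary analysis is | then |
|---|---|
| an analysis of imputed datasets (general rule) | MI under MAR is the primary analysis repeated, not a sensitivity analysis |
| the MMRM on observed data (model paragraph) | the imputed-datasets clause is wrong for the primary outcomes |
| the MMRM fitted to imputed datasets | comparing MMRM with MI no longer contrasts two methods |

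No reading leaves every sentence true, so one of them must change.

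**2. The plan's own figures.** The article gives no number on this point. The nearest is dropout: 166 / (1 − 0.20) = 207.5, rounded up to 208, which the planned 7 × 30 = 210 covers. At 20%, about 0.20 × 210 = 42 participants, or 21 per arm, would lack Week 12 data.

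**3. MI restricted to the MMRM's three time points.** Assumptions not in the article: SD 8, correlation 0.5, no true difference, 400 simulated trials, 20 imputations. Taken from it: 105 per arm. Week 12 is missing with logit(p) = −1.75 + 0.12 × (Day 30 score − 14), which gives 18.4% missing.

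- Likelihood estimate (stand-in for the MMRM): regress Week 12 on arm, baseline and Day 30 among the observed; fill missing values with predictions; take the arm effect adjusted for baseline.
- MI estimate: the same regression with parameters and residuals drawn at random, averaged over 20 imputations. As the number of imputations grows, this approaches the likelihood estimate.
- Result: correlation 0.995; mean absolute difference 0.08 points; standard error about 1.06.
- A separate simulation (150 trials, 22.7% missing, 50 imputations) gave correlation 0.999 and a mean difference of 0.05 against a standard error of 1.24.

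**4. What does move the estimate in that setting.** Worsening the missing MST scores by δ shifts the contrast by about δ × the proportion missing. For δ = 3: 3 × 0.184 = 0.55. Simulated: 0.49 − (−0.07) = 0.56. The comparison in step 3 cannot reveal a shift of this kind; an MNAR analysis can.

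**5. MI using visits the MMRM leaves out.** Of eight scheduled assessments the MMRM uses three, leaving those after sessions 3, 6 and 9 and at Weeks 4 and 8. Assumptions: 105 per arm, SD 8, correlations 0.5 except 0.8 between Weeks 8 and 12, about 19% missing, no true difference, 1,000 trials, and MST dropout that depends on a poor Week 8 score. The contrast is MST minus ECT, so negative values favour MST.

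- Three time points only: −0.68 (standard error 1.03).
- With Week 8 added: −0.02.
- Difference: −0.68 − (−0.02) = −0.66, or 0.66 / 1.03 = 0.64 of a standard error.

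A repeat run gave −0.66 and about 0. The size depends on how strongly dropout follows Week 8 and how closely Week 8 tracks Week 12. Both methods here are regression-based stand-ins, so the figures are illustrative.

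**The case against.** The strongest defence is that the imputation clause is a general statement made before any model is named. It never calls MI primary, and the more specific paragraph that follows should govern. MI also has legitimate uses here: an MMRM of a continuous score does not deal with missing covariates or with missing response and remission status. This has force and points to a sensible repair. But the clause is unrestricted, and the article nowhere confines it to those uses.

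A second defence is that the two estimates will hardly differ, so there is little to choose between. That is true in step 3 of the working but not in step 5, and the article does not say which situation applies.

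Three stronger readings are tempting and are not supported.

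- A reader might infer that agreement between MMRM and MI under MAR says nothing at all. That holds only if both use the same variables. With Weeks 4 and 8 in the imputation model, the comparison can expose a real problem, so deleting MI under MAR outright could discard a useful check.
- A reader might infer that the plan never departs from MAR. It does: "including multiple imputation (MI) under MAR and missing-not-at-random (MNAR) assumptions".
- A reader might fault the MNAR analysis for not being directed against MST. The article is silent on direction and size of shift, and such details may properly stand in an analysis plan that is not shown.

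**Conclusion.** The contradiction stands. The article assigns MI to the intention-to-treat analyses without restriction and also treats it as the alternative to an MMRM that already handles missing data. No analysis plan could follow both statements, so this is not a detail left to a fuller document. The primary HDRS-24 and HVLT-R estimates each have two candidate versions.

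On the HDRS-24 scale, the gap between them runs from under 0.1 points (same variables, ample imputations) to about 0.7 points (imputation using Week 8, with dropout in one arm driven by it). Both figures rest on assumed variances, correlations and dropout patterns. No comparable figure was worked out for HVLT-R. The working does not show that the trial's result will be biased. It shows that the primary analysis is unfixed and that one planned check may be uninformative. This should be corrected, but it does not undermine the design.

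**What to change.** 1. Name one primary analysis for both primary outcomes. One suitable choice is an MMRM under MAR fitted to all scheduled visits, with the treatment contrast at Week 12. This brings the intermediate scores into the primary model.
2. Remove the imputed-datasets clause from the general statement, or relabel it, for example by limiting it to missing covariates and to the response and remission outcomes.
3. Keep MI under MAR only if its imputation model uses information the MMRM does not, and say what that is. Do not present its agreement with the MMRM as evidence that MAR holds.
4. Let the MNAR analysis already planned carry the robustness claim. A series that worsens missing MST scores in steps would suit a non-inferiority question; this is a recommendation, not the correction of an error.

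The cost is wording in two places and slightly more analysis work. No new data are needed, because the additional visits are already scheduled.
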